### Statistical analysis plan

A statistical significant difference in mean change on MADRS-score, between study groups, from baseline to end of study, is the primary outcome measure of the study. The remaining clinical and biological measures are secondary outcome measures and will be analysed using the same approach as the primary outcome. To investigate the difference in response and remission rates between study treatments at week 20 and 24, logistic regression models will be applied to estimate the odds ratios. The definition of a “responder” is a person which symptoms of depression has dropped 50% in MADRS-score from baseline to week 20 or 24, and “remitters” are defined as MADRS score < 10 (Hawley et al. 2002) at week 20 or 24. Data analysis will be conducted by the authors and a statistician. Between-group comparisons will be performed by applying Student t-tests, Mann–Whitney U tests, Chi square tests or Fishers exact test, whichever is most appropriate. The primary analysis for primary and secondary outcomes will be based on an Intention-To-Treat (ITT) analysis comprise all study participants completed the baseline measurements. A generalized estimating equation (GEE) (Feng et al. 2001) approach will be taken, and the likelihood-based linear mixed effects repeated measures (LMERM) analyses (Mallinckrodt et al. 2001; Laird and Ware 1982) is the primary analysis. The LMERM-analysis includes the fixed variable *study treatment*, *visits* as factor variable, and *treatment*-*by*-*visits* interaction (intervention impact). The LMERM includes all available data at each time point and is the preferred methods of analysing clinical trial data in psychiatry due to the fact that likelihood approach deals with missing data in follow-ups assuming missingness is at random. Planned comparisons will be done with the LMERM models to determine between-group differences in score change from baseline to week 2, week 10, week 20 and week 24. Additional per-protocol analysis includes participants who completed the study intervention. Sensitivity analysis will evaluate missing at random assumptions for missing follow-up data. Missing data will be imputed assuming Missing Not At Random (MNAR) in intervention, control and both arms respectively and robustness of finding under different MNAR assumptions will be examined.

Additionally, effect sizes will be reported using Cohen’s guidelines (Cohen 1988). Dichotomous data will be presented as proportions, with 95% confidence interval, and reporting Chi square of Fishers’s exact p-value where appropriate. Likelihood based generalized linear mixed repeated measures approach (GLMRM) with logit link will be used to compare dichotomous outcomes.

All tests of treatment effects will be conducted using a two-sided alpha level of 0.05. The statistical analysis will be conducted utilizing the statistical software program STATA IC, version 15 (StataCorp. Stata Statistical Software: Release 15 College Station, TX: StataCorp LP 2017). Statistical analysis plans can be obtained from the first author ([name]).

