### Aims and objectives

The primary aim is to investigate the effects of adjunctive NAC treatment on depressive symptoms in participants diagnosed with bipolar depression. The secondary aims are to measure the biological effect of NAC treatment based on markers of oxidative stress in urine samples.

The study objectives are following:

#### Process aim 1

Assessing baseline adjusted between-group mean change between NAC and placebo group from baseline up till week 20 on The Montgomery–Asberg Depression Rating Scale score (MADRS) (Montgomery and Åsberg 1979).

#### Process aim 2

Assessing baseline adjusted between-group mean difference between NAC and placebo group from baseline up till week 20 on; the Bech-Rafaelsen Melancholia Scale (MES) (Bech 2002), the Young Mania Rating Scale (YMRS) (Young et al. 1978), the WHO-Five Well-being Index (WHO-5) (Staehr 1998), the Global Assessment of Functioning scale (GAF-F), The Global Assessment of Symptoms scale (GAF-S) (Jones et al. 1995) and the Clinical Global Impression-Severity scale (CGI-S) (Guy WNIoMHPRBECDEP 1976).

#### Process aim 3

Assessing baseline adjusted between-group mean difference between NAC and placebo group from baseline up till week 20 in urine samples to explore biological correlation in DNA and RNA damage by oxidative stress.

#### Process aim 4

Assessing baseline adjusted between-group mean difference between NAC and placebo group from baseline up till week 24 on MADRS, MES, YMRS, WHO-5, GAF-F, GAF-S, CGI-S and urinary markers.

#### Process aim 5

Assessing baseline urinary markers to explore correlation in DNA and RNA damage by oxidative stress and the degree of depression severity.

Additionally, blood samples and DNA are collected for further explorations towards detecting potential genetic polymorphisms related to oxidative defences, but are currently stored.

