### Sample size and feasibility of recruitment

The sample size estimation was based on prior data from a similar clinical trial showing mean (SD) in MADRS score (from baseline to end of the study (week 24)) was decreased by around 10.0 ± 4.3 and increased by around 0.9 ± 2.6 (in respectively the NAC and the placebo group (Berk et al. 2008). Our sample size was calculated using a two-tailed independent sample t-test with 80% power to detect baseline-adjusted between-group mean difference at week 20, and a two-sided alpha-level of 0.05. To detect a between-group mean difference of change from baseline of at least 8 ± 10.0, 56 participants in total were required. Due to the expectation of a 40% drop-out rate we aim to recruit an overall of 78 study participants. To achieve an adequate number of participants, all in- and out-patients from the Mental Health Service included in the study having a bipolar disorder or suspect to have this disorder, are offered to participate.

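### The aims and sample size promise a baseline-adjusted difference, but the terms listed for the primary mixed model give the unadjusted difference in mean change, which is unbiased but in large samples never more precise

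*Protocol article*

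**What the plan says.** Under Aims and objectives, Process aim 1 reads: "Assessing baseline adjusted between-group mean change between NAC and placebo group from baseline up till week 20". Process aims 2 to 4 use the same adjective for the secondary scales, the urinary markers and the week-24 comparisons. The sample size section repeats it, with "80% power to detect baseline-adjusted between-group mean difference at week 20". It does the calculation with a "two-tailed independent sample t-test", and states the effect as follows: "To detect a between-group mean difference of change from baseline of at least 8 ± 10.0, 56 participants in total were required".

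The Statistical analysis plan section names the likelihood-based mixed model for repeated measures as the primary analysis and spells out its terms: "The LMERM-analysis includes the fixed variable *study treatment*, *visits* as factor variable, and *treatment*-*by*-*visits* interaction (intervention impact". Between-group differences in change from baseline to weeks 2, 10, 20 and 24 are then taken from that model. Neither a baseline MADRS covariate nor a constraint of equal baseline means is mentioned. Secondary outcomes follow the same approach. ANCOVA is in the abbreviation list, but no analysis in the text uses it.

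**The concern.** The effect is described as baseline-adjusted in two places, and the model meant to produce it contains nothing that adjusts for baseline. If baseline is one of the visits and treatment has a free main effect, the treatment-by-visit contrast at week 20 is the difference between arms in mean change. If the response is already a change score with no covariate, the result is the same.

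Precision is at stake. A change score subtracts the whole baseline value, whereas an adjusted analysis subtracts only the part that predicts the outcome. The trial expects 40% drop-out from 78 participants, so it has little precision to spare. Because secondary outcomes inherit the method, the same loss can affect every secondary scale and urinary marker.

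**Working it through.** **Inputs from the article.** Difference in change 8, SD 10, 80% power, two-sided alpha 0.05, 56 participants before drop-out, 40% drop-out, 78 to recruit (Sample size section). Model terms: treatment, visit, treatment-by-visit (Statistical analysis plan). Entry at MADRS 18 or more (Inclusion criteria). Equal allocation is assumed, since no ratio is stated. The baseline SD, the week-20 SD and their correlation are not given, so every value below is an assumption.

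**The plan's own figure.** With d = 8/10 = 0.8, the two-sample t-test needs 25.5 per arm, so 26 per arm and 52 in total (50 by the normal approximation). The stated 56 is not reproduced. At 28 per arm, t-test power is 84%. This is a separate matter. What counts here is that the calculation uses an SD paired with a difference of change and no covariate, so it is an unadjusted change-score calculation despite its label.

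**What the listed model estimates.** On simulated complete data (28 per arm, five time points), the treatment + visit + treatment-by-visit model was fitted by generalised least squares under compound-symmetry, serial and unstructured covariance. The week-20 contrast was -1.4465 each time, identical to the raw difference in mean change.

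**Variance comparison.** Let s0 and s1 be the baseline and week-20 SDs and r their correlation.

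- Change score: s0² + s1² − 2·r·s0·s1
- Baseline-adjusted: s1²·(1 − r²)
- Change score minus adjusted: (s0 − r·s1)², which is never negative
- With s0 = s1, the ratio (adjusted/change) is (1 + r)/2

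| s0 | s1 | r | Change variance | Adjusted variance | Ratio |
|---|---|---|---|---|---|
| 10 | 10 | 0.3 | 140 | 91 | 0.65 |
| 10 | 10 | 0.5 | 100 | 75 | 0.75 |
| 10 | 10 | 0.7 | 60 | 51 | 0.85 |
| 8 | 10 | 0.5 | 84 | 75 | 0.89 |
| 6 | 10 | 0.3 | 100 | 91 | 0.91 |
| 5 | 10 | 0.3 | 95 | 91 | 0.96 |
| 5 | 10 | 0.5 | 75 | 75 | 1.00 |

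The rows with s0 below s1 represent an entry threshold that narrows the baseline SD. Two rows, (10, 10, 0.5) and (6, 10, 0.3), give a change SD of exactly 10. Both therefore fit the sample size section equally well, yet their ratios are 0.75 and 0.91.

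**Power at the expected number of completers.** 78 × 0.6 = 46.8, or about 23.4 per arm. Holding the change SD at 10, the effective standardised difference is 0.8/√ratio. Two-sided t-test:

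| Ratio | 1.00 (unadjusted, or no gain) | 0.91 | 0.85 | 0.82 | 0.75 | 0.65 |
|---|---|---|---|---|---|---|
| Power | 76% | 80% | 83% | 84% | 87% | 91% |

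**With drop-out.** A simulation of 78 participants (SD 10 at every visit, equal correlations, 40% randomly missing by week 20) compared the listed model with one constraining baseline means to be equal. Variance ratios were 0.75, 0.82 and 0.90 for correlations 0.3, 0.5 and 0.7. The gain is smaller than the complete-data formula gives (0.65, 0.75, 0.85), but it does not vanish. The completer power figures are therefore approximate.

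**The case against.** The strongest reply is that the article uses baseline-adjusted to mean change from baseline. Process aim 1 attaches the adjective to a mean change, the sample size section computes the quantity with a t-test and then restates it as a difference of change, and the planned comparisons are in score change. On that reading, aims, sample size and model agree and the fault is one of wording. This may well be what was meant. It leaves the wording to be corrected and does not remove the efficiency point.

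A second reply is that the article is condensed and says analysis plans can be obtained on request, so a covariate may be specified there. That is possible. But the article does list the model's terms, and the list leaves out what its own objectives call for.

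Four stronger readings are tempting, and the documents support none of them:

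- **The analysis estimates something other than the stated objective.** Under randomisation, the change-score and adjusted contrasts target the same mean treatment difference. They differ in precision.
- **Chance baseline imbalance distorts the result as a further harm.** Over randomisation the estimate is unbiased, and chance imbalance is already part of the change-score variance. Listing it separately counts the same loss twice.
- **The sample size is too small because of this.** The SD of 10 is stated with a difference of change, so the calculation already matches an unadjusted analysis.
- **Leaving out inclusion site is an error.** No stratification by site is described under Randomization, so no stratification factor has been omitted. Adjusting for site is optional.

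**Conclusion.** The point holds as a mismatch of wording and model, with an avoidable and uncertain loss of precision. The aims and sample size sections name a baseline-adjusted effect, and the listed primary model gives the unadjusted difference in mean change. Validity is not in question.

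The loss cannot be fixed from the article. With equal SDs and correlations of 0.3 to 0.7, adjustment would cut the variance to 0.65 to 0.85 of the change-score value. If the entry threshold narrows the baseline SD, the ratio is about 0.9 to 1.0. For a difference of 8 and a change SD of 10, the gain over the unadjusted 76% is therefore nil at worst, about 4 points at ratio 0.91 and about 11 points at 0.75. The larger gain should not be quoted alone, because the smaller one is equally compatible with the stated SD. That adjustment never increases the variance is a large-sample result.

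**What to change.** Specify the primary model with the pre-treatment MADRS as one of the responses, visit as a factor, treatment-by-visit terms at the post-baseline visits only, and baseline means constrained equal across arms. This keeps everyone in the intention-to-treat set, which the plan defines as all who completed the baseline measurements. Table 1 marks MADRS at screening and not at week 0, so the text should name the screening score as baseline.

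An alternative is to model post-baseline MADRS (weeks 2, 10, 20, 24) with baseline and baseline-by-visit as covariates, plus treatment, visit and treatment-by-visit. This is not strictly equivalent, because participants with no post-baseline visit drop out of it, and the text should say so.

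Use the same form for each secondary scale and urinary marker, with its own baseline. If the sponsor prefers the unadjusted model, the term baseline-adjusted should be replaced in the aims and the sample size section by difference in change from baseline.

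The cost is wording only, since Table 1 already schedules the pre-treatment measurements. The choice should be fixed before unblinding so that it cannot depend on the results.

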## Discussion

In the current study, we will investigate the clinical effect of 3 g/day of adjunctive NAC treatment on symptoms of bipolar depression utilizing a randomized, double-blinded, parallel group, placebo-controlled design. People diagnosed with bipolar disorder predominantly experience depression, which is currently challenging to treat (Grande et al. 2016). It is evident that a large group of patients do not respond adequately to traditional pharmacotherapy and/or psychotherapy, which creates a need for novel treatment opportunities. If this trial indicates that NAC treatment significantly reduces symptoms of depression, NAC may become an important part of the pharmacotherapeutical options for bipolar disorder.

NAC is well-tolerated with few and often mild adverse events (Fernandes et al. 2016), and is available without prescription in many countries. The selected dosage in this trial has been well-tolerated in previous trials (Prado et al. 2015; Mardikian et al. 2007). NAC is hypothesized to decrease symptoms of depression at least in part due to its antioxidant properties. At present, few studies have investigated the effects of NAC in patients with bipolar depression, and the results have been mixed. Our study therefore will add to the limited clinical database (Berk et al. 2008, 2012).

The main strengths of the trial are the double-blinded design, with only two raters, and the possibility to do the study interviews in the patients’ home, which should reduce drop-outs.

To increase adherence, the study medication is formulated as tablets instead of effervescent tablets, making is possible to take it along with existing medication. To reflect usual clinical practice, all kinds of non-study pharmaceutical treatment are allowed, including changes prior to and after inclusion. However, this may diminish the chances to detect a potential superiority of NAC over placebo.

The novelty of this study is the collection of several biological materials to explore the oxidative balance, inflammation and DNA damage related to the disorder and the treatment. Additionally, the study will shed light on the possible immune modulatory effects of NAC treatment. The markers may provide an insight to the potential mechanisms underlying the pathophysiology of BD.

### Dissemination of results

The results from this study will be presented at national and international conferences and published in peer-reviewed journals.

## Abbreviations

AE: adverse events
ANCOVA: ANalysis of COVAriance
AR: adverse reactions
CGI-S: Clinical Global Impression Scale-Severity scale
CONSORT: The Consolidated Standards of Reporting Trials
CRF: Case Report Form
[name]: [name]
DSM-IV: Diagnostic and Statistical Manual of Mental Disorders 5
ECT: electroconvulsive therapy
GAF-F: Global Assessment of Functioning Scale
GAF-S: Global Assessment of Symptoms Scale
GCP: good clinical practice
GDP: good distribution practice
GEE: generalized estimating equation
GMP: good manufacturing practice
GSH: glutathione
[name]: [name]
[name]: [name]
ITT: intention to treat
LMERM: linear mixed effects repeated measures
MADRS: Montgomery–Asberg Depression Rating Scale
[name]: [name]
MES: Melancholia Scale
M.I.N.I-interview: Mini International Neuropsychiatric Interview
MNAR: missing nor at random
NAC: *N*-acetylcysteine
[name]: [name]
[name]: [name]
REDCap: research electronics data capture
[name]: [name]
[name]: [name]
SAE: serious adverse event
SAR: serious adverse reaction
SPIRIT: The Standard Protocol Items: Recommendations for Intervention Trials
WHO-5: WHO-5 Well-Being Index
YMRS: Young Mania Rating Scale
